#### Secondary outcomes

7.11.2

##### HPV positivity rate and subsequent treatment adherence

7.11.2.1

The HPV positivity rate, defined as the proportion of participants testing positive for HPV through self-sampling, will be calculated based on laboratory-confirmed results using standardized PCR techniques. Data will be collected from certified laboratories, with a subset of samples retested for validation. Subsequent treatment adherence will be assessed by tracking participants’ attendance at recommended follow-up appointments and receipt of appropriate treatments following a positive HPV result. This will be monitored through electronic medical records and phone follow-ups at 1 and 3 months post-notification. Adherence will be recorded as a binary outcome and expressed as a percentage of participants who follow through with recommended care.

##### Willingness to accept HPV self-sampling

7.11.2.2

Types of self-sampling tools participants are familiar with, whether they have previously used self-sampling methods for health monitoring, acceptance of the self-sampling intervention concept, and self-assessed ability to perform the self-sampling process. This aspect aims to understand factors hindering women from using self-sampling kits for HPV testing. Factors may include concerns about the accuracy of self-sampling, discomfort or lack of confidence in performing the sampling process, and reluctance to engage in self-sampling due to cultural or personal preferences. Additionally, barriers such as limited access to follow-up healthcare services, lack of awareness about the importance of HPV screening, and logistical challenges in returning the samples to the laboratory will also be explored.

Wu Xueqin’s self-administered questionnaire: Cervical Cancer Knowledge Questionnaire was used to investigate the subjects’ knowledge of cervical cancer, which consisted of 15 questions, all of which were single-choice questions, of which the first question was a jumping question, and if you chose “no”, you did not need to answer the second to fifteenth questions.1 point was scored for correctly answering questions 2-15, and 0 point for wrongly choosing or not knowing, out of 14 points. Questions 2–15 were scored as “1” if they were correctly selected, and “0” if they were incorrectly selected or not known, with a full score of 14. A score of ≥8 was defined as knowledge of cervical cancer according to the cut-off of 60% of the total score (10*60% = 8.4 points, rounded up to 8 points), with the rate of knowledge = number of people who were aware of the knowledge/number of people who responded to the questions*100%.Wu Xueqin’s self-administered questionnaire: Cervical Cancer Screening and HPV Vaccination Attitude Scale was used to investigate subjects’ attitudes toward cervical cancer screening and HPV vaccination, which was measured using a 5-point Likert scale, with scores of 5, 4, 3, 2, and 1 corresponding to “Strongly Agree”,”Agree “, “Can’t say”, “Disagree”, and “Strongly Disagree”, respectively; negative scoring was applied to the barrier perception dimension, i.e. scores 1, 2, 3, 4, and 5 correspond to “strongly agree”, “agree”, “can’t say”, “disagree”, and “strongly disagree”, respectively. The higher the score, the more positive the attitude towards screening or vaccination. Screening rate = number of people screened/number of people in the group participating in the survey*100%, and the same for vaccination rate.

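### The knowledge cut-off contradicts its own rule (8 of 14 is 57.1%, below the stated 60%), and the rate's denominator does not say how women who skip the test are counted

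*Protocol article*

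**What the plan says.** Section 7.11.2.2 describes a 15-item knowledge questionnaire. Question 1 is a filter: "if you chose “no”, you did not need to answer the second to fifteenth questions". Questions 2 to 15 earn 1 point if correct and 0 if wrong or not known, "with a full score of 14".

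The classification is then fixed: "A score of ≥8 was defined as knowledge of cervical cancer". The reason given is that this was set "according to the cut-off of 60% of the total score (10*60% = 8.4 points, rounded up to 8 points".

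The knowledge rate is defined as "number of people who were aware of the knowledge/number of people who responded to the questions*100" (a percentage).

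Table 1 in Section 7.12 lists the knowledge scale under a heading marked as a secondary outcome. It is taken from the baseline questionnaire and ticked at baseline only.

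**The concern.** The sentence that sets the cut-off gives a base of 10 for a scale whose maximum is 14, and a rounding direction that does not lead to the number printed. The criterion (60% of the total) and the operating rule (8 or more) therefore disagree about a woman who scores exactly 8. Two analysts could apply 8 or 9 and both cite the same sentence.

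The rate has a second loose end. Women who answer no to question 1 give no answers to the scored items. The text assigns 0 to wrong and not-known answers but does not mention items passed over by the jump, and it does not say which questions a woman must have answered to enter the denominator.

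At stake is the reported knowledge rate of the sample, a figure that Table 1 places among the secondary outcomes.

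**Working it through.** **Inputs, all from Section 7.11.2.2.** Maximum score 14 (questions 2 to 15, one point each); criterion 60% of the total; printed product 8.4 from a base of 10; stated rounding up; cut-off applied 8 or more.

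**Step 1: reproduce the printed product.**
- Base 10, as printed: 10 x 0.60 = 6.0
- Base 14, the full score: 14 x 0.60 = 8.4
- Base 15, all questions: 15 x 0.60 = 9.0

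Only base 14 gives 8.4. The printed 10 is therefore wrong and is probably a slip for 14.

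**Step 2: reproduce the rounding.** 8.4 rounded up is 9; to the nearest whole number it is 8; rounded down it is 8. The stated direction does not give the stated result.

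**Step 3: compare whole scores with the criterion.**
- 8/14 = 57.1%, below 60%
- 9/14 = 64.3%, the first whole score to reach 60%

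**Step 4: size of the cut-off effect.** The document gives no score distribution, so this step rests on an assumption: 14 independent items with a common probability p of a correct answer. The difference between the two cut-offs is then the share scoring exactly 8, which is C(14,8) p^8 (1-p)^6 with C(14,8) = 3003. At p = 0.5 this is 3003/16384 = 18.3%.

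| Assumed p | Score 8 or more | Score 9 or more | Difference (points) |
|---|---|---|---|
| 0.4 | 15.0% | 5.8% | 9.2 |
| 0.5 | 39.5% | 21.2% | 18.3 |
| 0.6 | 69.2% | 48.6% | 20.7 |
| 0.7 | 90.7% | 78.1% | 12.6 |
| 0.8 | 98.8% | 95.6% | 3.2 |

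**Step 5: size of the denominator effect, if skippers are left out.** Let r be the rate among women who answer the scored items and s the share who answer no to question 1. Leaving skippers out reports r. Keeping them in as not knowledgeable reports r(1-s). The ratio is 1/(1-s). The document gives no value for s. For assumed s of 10%, 20% and 30% the ratio is 1.11, 1.25 and 1.43. With r = 50%, also assumed, a reported 50% would stand against 45%, 40% and 35%. If skippers are already kept in as not knowledgeable, there is no inflation.

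**The case against.** **The cut-off of 8 may be intended.** The operating rule is stated plainly, and 8 is what rounding 8.4 to the nearest whole number gives. The slip may lie only in the printed 10 and in the word up. The questionnaire is attributed to a named developer whose own scoring rule is not in the document. This stands as a reason not to insist on 9. It does not rescue the sentence: scores are whole numbers, and a score of 8 misses a 60% criterion whichever way 8.4 is rounded. Either the cut-off or its justification has to change.

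**The denominator may be sound.** A reader might infer that women who skip do leave the denominator, so that the rate is overstated on two counts. The text does not establish this. Question 1 is one of the 15 questions, so a woman who answers no has responded to a question. Two features favour exclusion: the scored questions are exactly the ones skippers do not answer, and the same section words the screening-rate denominator differently, as survey participants in the group. These make exclusion plausible, not certain. What question 1 asks is not shown either, so calling skippers the least knowledgeable women is a reasonable guess and no more.

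**The consequences are small.** Section 7.6 places randomization after the baseline visit, and Table 1 collects the scale at baseline only. It therefore cannot carry an intervention effect. A reader might also infer that knowledge will serve as a covariate or subgroup for the feedback rate, but Table 1 names only sociodemographic and behavioral information as covariates. This objection stands and limits the weight of the point.

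**Conclusion.** The cut-off sentence is wrong as written. The base should be 14, 8.4 rounded up is 9, and a score of 8 (57.1%) fails the 60% criterion it is said to meet. Measured against that criterion, women scoring exactly 8 are counted as knowledgeable although they fall short, and the reported rate is higher than it should be. The size depends on how many women score 8: about 3 to 21 percentage points under the independent-items assumption with p from 0.4 to 0.8.

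It would go too far to say that every woman scoring 8 is certainly misclassified. That holds only if the 60% rule governs; a validated cut-off of 8 in the source questionnaire would make the justification the error.

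The denominator is an ambiguity, not a demonstrated error. An inflation of 1.11 to 1.43 follows only if skippers are excluded and their share is the assumed 10% to 30%.

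This is a minor correction to a baseline-only measure. The primary outcome (Section 7.11.1), the sample size (Section 7.5) and the comparison between the groups are unaffected.

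**What to change.** 1. Correct the formula to 14 x 60% = 8.4 and set the cut-off at 9 or more (9/14 = 64.3%). Alternatively, if the source questionnaire has a validated cut-off of 8, keep 8, cite that source, and remove the statement that it represents 60% rounded up.
2. State how a no to question 1 is handled. The clear rule is to score these women 0 of 14 and keep them in the denominator, so that it covers every woman who answered question 1. This presumes that a no there signals lack of awareness, which the sponsor can confirm from the questionnaire.

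The cost is one corrected line and one scoring sentence, with no change to data collection. The reported knowledge rate will be lower if the cut-off moves to 9, or if skippers would otherwise have been left out.

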##### Psychological and behavioral health

7.11.2.3

To assess the severity of anxiety symptoms experienced by participants over the past two weeks, the Generalized Anxiety Disorder-3 (GAD-3) scale will be utilized. This is a shortened version of the GAD-7, comprising three items rated on a four-point scale (0 = “not at all”, 1 = “several days”,2 = “more than half the days”, 3 =“nearly every day”). Total scores range from 0 to 9, with higher scores indicating greater anxiety levels (0-2 = no significant anxiety, 3-5 = mild anxiety, 6-7 = moderate anxiety, 8-9 = severe anxiety).

The Perceived Stress Scale (PSS) will evaluate the degree of perceived stress in participants’ lives, particularly in situations they find unpredictable, uncontrollable, or overloaded. The scale includes four items, each rated on a five-point Likert scale (0 = “never” to 4 = “very often”). Two items are scored as forward scoring questions (1, 4), and two as reverse scoring questions (2, 3). Higher scores reflect higher perceived stress, with a Cronbach’s alpha coefficient of 0.754.

The Family Health Scale Short-Form (FHS-SF) will measure maternal family health functioning across four dimensions: family/social/emotional health processes, family healthy lifestyle, family health resources, and external social support. The scale consists of 10 items, each scored on a five-point scale (1 = “strongly disagree” to 5 = “strongly agree”), with items 6, 9, and 10 reverse scored. Higher total scores indicate better maternal family health, with a Cronbach’s alpha coefficient of 0.846.

Health literacy will be assessed using the Health Literacy Scale (HIS), a four-item multiple-choice questionnaire divided into three dimensions: health care, disease prevention, and health promotion. Responses are categorized as very easy, easy, difficult, or very difficult.

The New General Self-Efficacy Scale (NGSES-SF) will measure psychological dimensions across three aspects: level or degree, intensity, and prevalence, with response options ranging from strongly disagree to strongly agree.

Social support levels will be evaluated using the Perceived Social Support Scale-Short Form (PSSS-SF), a three-item version of the original PSSS. This scale assesses overall perceived social support from family, friends, and significant others on a 7-point Likert scale (1 = “not at all compatible” to 7 = “fully compatible”). Total scores range from 3 to 21, with higher scores indicating greater perceived social support (3-9 = low support, 10-17 = moderate support, 18-21 = high support).

Personality traits will be assessed using the Chinese Big Five Personality Inventory Brief Version (CBF-PI-B), which evaluates five dimensions: neuroticism, extraversion, openness, agreeableness, and conscientiousness. Each dimension is represented by a single item rated on a 6-point scale (1 = “not at all” to 6 = “fully”), providing a quick assessment of key personality traits.

Depression severity will be measured using the Patient Health Questionnaire-9 (PHQ-9), a nine-item tool corresponding to DSM-5 criteria for major depressive disorder. Each item assesses the frequency of depressive symptoms over the past two weeks on a 4-point scale (0 = “not at all” to 3 = “nearly every day”). Total scores range from 0 to 27, with higher scores indicating greater depression severity (0-4 = minimal depression, 5-9 = mild depression, 10-14 = moderate depression, 15-19 = moderately severe depression, 20-27 = severe depression).

### Follow-up

7.12

This is a six-month study and the intervention will be implemented during the first four weeks of subject enrollment. All subjects participating (both the “Pay-It-Forward” group and control group) are required to finish electronic questionnaires at two time points, including baseline and post intervention. The content of the follow-up visits varied across time points, with sociodemographic information and baseline health data collected only at baseline. Behavioral information, HPV self-sampling results, and participant satisfaction data will be collected at the 4-week post-intervention follow-up point. The specific follow-up and related data collection schedule is shown in **Table 1**.

**Table 1 T1:** Variables and measures collected at every time points.

Variables		Date source	Study Period	Baseline (T0)	Post-intervention (T1)
			timepoint	0w ± 1w	4w ± 1w
Intervention preparation	\	\	Informed consent	✓	\
	\	\	Random grouping	✓	\
	\	\	Online consulting service	✓	✓
Covariates	Individual	Baseline questionnaire	Sociodemographic information	✓	\
	Individual	Baseline questionnaire and Follow-up questionnaire	Behavioral information	✓	✓
Primary outcome	Feedback rate of HPV self-sampling	Laboratory records	Percentage of participants who return the HPV self-sampling kit within 1 month	\	✓
HPV infection status (Secondary Outcome)	HPV positivity rate	Laboratory records	Proportion of participants with lab-confirmed HPV-positive results (PCR testing)	\	✓
HPV self-sampling cognition and acceptance (Secondary Outcome)	HPV Self-Sampling Awareness	Follow-up questionnaire	HPV Self-Sampling Awareness Questionnaire	\	✓
	HPV self-sampling Satisfaction	Follow-up questionnaire	HPV self-sampling Satisfaction Questionnaire	\	✓
	HPV Self-Sampling Acceptance	Follow-up questionnaire	HPV Self-Sampling Acceptance Scale	\	✓
Cervical cancer health literacy and attitudes (Secondary Outcome)	Cervical Cancer-related Knowledge	Baseline questionnaire	Cervical Cancer-related Knowledge Scale	✓	\
	Cervical Cancer Screening and HPV Vaccination Attitude	Baseline questionnaire	Cervical Cancer Screening and HPV Vaccination Attitude Scale	✓	\
Psychology status (Secondary Outcomes)	depressed	Baseline questionnaire	PHQ-9	✓	\
	Anxiety	Baseline questionnaire	GAD-3	✓	\
	Stress	Baseline questionnaire	PSS-4	✓	\
	Family health	Baseline questionnaire	FHS-SF	✓	\
	Social support	Baseline questionnaire	PSSS-SF	✓	\
	personalities	Baseline questionnaire	BFI	✓	\
Health status(Secondary Outcomes)	health awareness	Baseline questionnaire	HLS	✓	\

The full name of PHQ-9 is Patient Health Questionnaire-9 Scale; The full name of GAD-3 is Generalized Anxiety Disorder scale; The full name of PPS-4 is Perceived Stress Scale; The full name of FHS-SF is The Family Health Scale short-form; The full name is HLS is Health Literacy Scale; The full name of PSSS-SF is Perceived Social Support Scale; The full name of BFI is The big five inventory.

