### Sample size

7.5

The primary outcome is the feedback rate of HPV self-sampling. According to the results of previous studies (9), we hypothesize that the “Pay-It-Forward” intervention will increase the feedback rate to 90%, the feedback rate of HPV self-sampling results in the control group is 61.7%. Using the PASS 15.0 software and applying a two-sided test with α = 0.05 and a power of the test (1 - β) = 0.80, the required sample size per group was calculated to be 86 participants. Considering a potential dropout rate of 20%, we ultimately determined that 54 participants should be recruited per group, resulting in a total sample size of 108 participants.

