### Interventions

7.7

Compared with the control group, the intervention frequency is only once. That is, when distributing the HPV self-sampling kit, the intervention group needs to prepay to obtain the kit, while the control group can receive the HPV self-sampling kit without payment. Considering that the market price of an HPV self-sampling kit is around 20 RMB, we set the prepayment fee at 20 RMB. This can well simulate the real situation when the participants purchase the kit by themselves in daily life. Moreover, a proper deposit can avoid the problems caused by a high deposit: ① exceeding the participants’ affordability and thus reducing their willingness to participate; ② increasing the participants’ psychological pressure and causing unnecessary worries, which may affect the accuracy of the study results. On the other hand, a proper deposit can also avoid the problems caused by a low deposit: lack of effective constraints, leading to participants not taking the trial seriously and thus causing unstandardized sampling operations and other problems that may affect the trial results. We use the deposit as an incentive to encourage participants to actively provide feedback on the results of HPV self-sampling and to increase the feedback rate of HPV self-sampling results. The intervention flow chart is shown in **Figure 2**. To enhance participants’ psychological commitment and ensure active participation, the full prepayment amount will be refunded upon completion and feedback of the self-sampling results. Participants can choose from various convenient payment methods, including cash, bank transfer, or third-party payment platforms, to minimize payment costs and barriers. After self-sampling, participants in the intervention group can return the sampling kit to the corresponding Maternal and Child Health Care and Family Planning Service Center, which will then forward it to the Genetic and Eugenics Office of the Inner Mongolia Maternal and Child Health Care Hospital. A dedicated hotline will be established to facilitate timely feedback from participants. For those with positive HPV results, free follow-up medical services, including physician consultations and examination appointments, will be provided to ensure they receive proper treatment. Additionally, ongoing monitoring of participants’ adherence to treatment will be conducted.

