#### Primary outcome

7.11.1

The primary outcome of this study is the feedback rate of HPV-based self-sampling. It refers to the percentage of participants who mail back the tested HPV sampling kits to us within 1 month after receiving the HPV self-sampling kits, relative to the total number of HPV self-sampling kits distributed. If the feedback is not received within 1 month after distribution, it is considered as no feedback by default.

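### The required T1 questionnaire on self-sampling may be given from day 21, before the 1-month return window of the primary outcome closes, so it may prompt late returns in both arms and modestly dilute the difference

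*Protocol article*

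**What the plan says.** **Return window.** Section 7.11.1 defines the primary outcome as the percentage of participants who send the kit back "within 1 month after receiving the HPV self-sampling kits, relative to the total number of HPV self-sampling kits distributed". It closes the window firmly: "If the feedback is not received within 1 month after distribution, it is considered as no feedback by default".

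**Follow-up questionnaire.** Section 7.12 states that all participants in both groups are "required to finish electronic questionnaires at two time points, including baseline and post intervention". Having returned the kit is not a condition. The text adds that "participant satisfaction data will be collected at the 4-week post-intervention follow-up point". Table 1 gives T1 as 4 weeks ± 1 week, counted from a baseline at week 0. The instruments ticked at T1 include an awareness questionnaire, the "HPV self-sampling Satisfaction Questionnaire" and an acceptance scale, all about self-sampling. Table 1 also lists the 1-month primary outcome under T1.

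**Planning rates.** Section 7.5 assumes feedback of 90% in the deposit arm and 61.7% in the free-kit arm, with a two-sided α of 0.05, power of 0.80 and 54 women per group.

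Nothing in the article holds T1 back until the return window has closed.

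**The concern.** The primary endpoint is a behaviour: remembering to use a kit and taking the trouble to send it back. The contrast of interest is a deposit against free distribution. A compulsory questionnaire about self-sampling that reaches a woman with an unused kit and days still to run is a plausible cue to act. If it works as a cue, the trial estimates the deposit effect in the presence of a later study contact, and not the effect of the deposit under plain distribution.

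The planned rates suggest the likely direction. Non-returners are expected to be 38.3% of the free-kit arm and 10% of the deposit arm, so an equally effective cue would raise the free-kit rate more and bring the arms closer.

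There is also a bookkeeping problem. For a woman seen at T1 on days 21 to 27, the outcome listed at that visit is still open under any definition of a month. She could also be asked about her satisfaction with a procedure that she has not yet carried out but may yet carry out in time.

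**Working it through.** **Timing**
- T1 opens on day 28 − 7 = 21 and closes on day 28 + 7 = 35, which is 15 permitted days (Table 1).
- The return window ends 28 to 31 days after kit receipt, depending on how a month is counted (section 7.11.1). T1 can therefore open 7 to 10 days before it ends.
- With a month taken as 30 days (assumption), days 21 to 29 come before the deadline: 9 of 15, or 0.60.

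**The plan's own sample size**
- Rates of 0.617 and 0.90, two-sided α 0.05 and power 0.80 give 35 per group by the pooled-variance formula and 42 with continuity correction.
- Allowing for 20% dropout, 42 / 0.8 = 52.5, rounded up to 53. This is close to the stated 54.
- The intermediate figure of 86 fits only as a total (43 per group; 43 / 0.8 = 53.75, rounded up to 54), not as a per-group number. That is a separate matter. The planning rates used below are unaffected.

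**Effect of a cue**

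Let p be the fraction of non-returners who return because of the contact, equal in both arms, and f the share of women contacted before the deadline. Neither is given in the documents.
- Free-kit rate = 0.617 + f·p × 0.383
- Deposit rate = 0.90 + f·p × 0.10
- Difference = 0.283 × (1 − f·p)

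Power uses the two-proportion normal approximation without continuity correction: Φ[(d − 1.96·SE₀)/SE₁], with SE₀ pooled and SE₁ unpooled. With no cue and 54 per group, SE₀ = 0.0824 and SE₁ = 0.0777, so (0.283 − 0.1614)/0.0777 = 1.56 and power is 94%.

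| p (assumed) | Difference, even spread (f = 0.60) | Power, 54 per group | Difference, all contacted early (f = 1) | Power, 54 per group |
|---|---|---|---|---|
| 0 | 28.3 | 94% | 28.3 | 94% |
| 10% | 26.6 | 92% | 25.5 | 91% |
| 20% | 24.9 | 90% | 22.6 | 86% |
| 30% | 23.2 | 87% | 19.8 | 79% |

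Example at p = 20%, even spread: 28.3 × (1 − 0.60 × 0.20) = 28.3 × 0.88 = 24.9.

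The length of the month matters little. At p = 20% with an even spread, a 28-day month (f = 7/15) gives 28.3 × 0.907 = 25.7 points, and a 31-day month (f = 10/15) gives 28.3 × 0.867 = 24.5.

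For any given p, the f = 1 columns are an upper bound on the loss, because they treat every non-returner as contacted in time.

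**Direction**

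The ratio of expected non-returners is 38.3 / 10 = 3.83. The difference fails to shrink only if deposit-arm non-returners respond at least 3.83 times as strongly. For instance, conversion of 10% in the free-kit arm and 40% in the deposit arm gives 94.0% − 65.5% = 28.5 points.

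**The case against.** The strongest reply is that the article gives no dispatch day, does not call the questionnaire a reminder, and describes in section 7.14 only an online form opened by QR code. T1 is labelled post-intervention and carries the 1-month outcome, so it may be meant to close the return window, with ± 1 week as an ordinary visit tolerance. Section 7.12 also puts the intervention in the first four weeks and the follow-up 4 weeks after it, which could be read as about week 8. These readings are possible. But Table 1 counts 4 weeks from week 0, and section 7.7 places the intervention at the single moment when the kit is handed out, so day 21 is the better-supported reading. If another was meant, Table 1 needs correcting anyway.

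The reply is right on size. Non-return counts as no feedback and the denominator is kits distributed, so all 54 women per arm count. With an even spread of contacts, power stays above the planned 80% throughout the range shown. A woman contacted on day 28 or 29 also has little time to sample and be counted. Deposit-arm women have 20 RMB awaiting refund and might respond more strongly, so equal p is an assumption, although reversing the direction takes nearly a fourfold gap.

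Three stronger readings that a reader might infer are not supported:
- **T1 is an established second intervention that does shrink the effect.** The documents show an overlap of windows, not a response to it.
- **T1 contradicts section 7.7.** The words "Compared with the control group, the intervention frequency is only once" concern the prepayment at kit distribution. A questionnaire does not conflict with them.
- **One arm may be contacted earlier, which would bias the contrast.** Table 1 gives both arms the same window, and nothing suggests different handling.

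**Conclusion.** The point holds as a timing overlap between two windows that the article itself states. A required questionnaire on the target behaviour may be given up to 7 to 10 days before the primary outcome closes, and that outcome is listed at a visit that can come before its own deadline.

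The consequence is conditional and modest. For p between 10% and 30%, equal in both arms, the loss is about 1.7 to 5.1 points with contacts spread evenly (28.3 − 26.6 and 28.3 − 23.2), and at most 2.8 to 8.5 points if every contact is early (28.3 − 25.5 and 28.3 − 19.8). These figures rest on the assumed p, the 30-day month, and the use of final non-return rates as a stand-in for the unknown number of kits outstanding at contact.

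Because both arms receive the same contact, type I error is not inflated. The risk is some dilution, and an estimate that does not describe distribution without a later contact.

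**What to change.** In section 7.12 and Table 1, open the T1 questionnaire and any study-initiated T1 contact only after the woman's own return window has closed, identically in both arms. State 1 month as a number of days. With 30 days, T1 could run on days 31 to 38 after kit receipt. Add that the study initiates no contact mentioning the kit before then.

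For women already enrolled, record the date of first T1 contact (not the date of completion) and add a sensitivity analysis that counts only returns before that contact. This shortens the window by a varying number of days, so it is a check beside the primary analysis and not a replacement for it.

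The cost is a shift of the T1 window by up to about ten days at its opening and slightly older recall of the sampling experience. In return, the 1-month outcome is settled for every woman by T1.
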